### Economic evaluation

The economic evaluation will be conducted from a health funder plus patient perspective. The ‘within trial’ economic evaluation will include a cost-effectiveness and a cost-utility analysis.

The cost of delivering the intervention, including setting up the technology platform, delivery of text messages, staffing costs and consumables, will be determined using standard micro-costing techniques. Healthcare utilisation, including doctor or specialists visits, will be determined by individual data linkage to the Medicare Benefits Schedule. Medicines use will be determined from the Pharmaceutical Benefits Schedule. Individual patient consent will be obtained to access records from these administrative databases. The records will provide both health funder (government) cost and patient out-of-pocket costs. All costs will be valued in 2018 Australian dollars.

The main outcome for the cost-effectiveness analysis will be the incremental cost of the intervention per unit of HbA1c avoided compared with usual care. The cost-utility analysis will estimate the incremental cost per quality adjusted life year (QALY) gained. Quality of life will be measured using the SF12v2 at baseline and end of trial and quality adjusted life years calculated using the United Kingdom valuation [58].

Using the mean costs and mean health outcomes in each trial arm, incremental costs and incremental outcomes will be determined. These results will be plotted on a cost-effectiveness plane with bootstrapped estimates to present joint uncertainty in costs and health outcomes. Multiple one-way sensitivity analyses will be conducted around key variables. A cost-effectiveness acceptability curve (CEAC) will be derived which estimates the probability of the intervention being cost-effective at different willingness to pay thresholds.

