The text message intervention will consist of daily text messages for months 1–3; and four messages per week for months 4–6. The messages will be designed to be sent at random times between 8 am and 5 pm, with message themes coinciding with relevant times of the day e.g. breakfast messages sent in the early morning, healthy dinner options sent in the afternoon. They include modules on nutrition, physical activity and sedentary behaviour, diabetes care and compliance with the diabetes Annual Cycle of Care, weight management, medication adherence and smoking cessation. The messages will be semi-personalised with occasional use of the participant’s name receiving the messages, occasional use of the researcher’s name ([name]) sending the messages, and tailored so that only smokers receive smoking cessation messages and only those taking medication will receive medication adherence messages (see Table 1).

**Table 1 Tab1:** Summary of the 6 month DTEXT intervention

Module	Description	Number of Messages n (%)	Example message
Nutrition	Up to 3 messages a week on dietary advice and recommendations; eating out; portion size; example meal, snack and drink options.	47 (35)	For good health, aim to eat 5 serves of vegetables each day. 1 serve = half a cup cooked vegetables or 1 cup salad vegetables. Try eating some with each meal.
Physical activity	Up to 3 messages a week on physical activity advice and recommendations; reducing sedentary time; goal setting; free or home based activities; community programs and support.	47 (35)	Hi (name), Did you know by walking up 2 flights of stairs per day you can lose 3 kg a year? Are there any stairs nearby you could try? [name]
Diabetes care	Up to 2 messages per week on: self-management; completing the Annual Cycle of Care; and accessing health professionals for care and support.	26 (20)	HbA1c tests are the best measure of your diabetes control. Aim to keep HbA1c under 7% or 53 mmol and have it tested each year. Ask your doctor about your HbA1c.
Weight management	Up to 1 message per week with motivation and guidance to achieve and maintain a healthy weight range.	13 (10)	Sugary drinks (soft drink, sports drink, cordial) can lead to weight gain – a 600 ml soft drink bottle has 16 teaspoons of sugar!

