#### Secondary outcomes

Secondary outcome measures will be collected at baseline, 3 and 6 months through objective measures taken by pathology collectors and a self-report telephone questionnaire administered by the research team. The questionnaire was piloted with 10 people and determined to be acceptable by pilot participants and easy to deliver with an appropriate timeframe (10–15 min) by the research team.

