##### Quality of life

This will be assessed using the Short Form 12-item Health Survey (SF12v2). This multi-purpose survey measures quality of life in terms of functional health and wellbeing and has two subscales addressing psychometric measures of physical and mental health [57]. Preference-based health utilities will be determined from a subset of the SF12 questions, using the UK valuation algorithm [58]. These utility scores will be used to calculate Quality-adjusted Life Years (QALYs) for the economic evaluation.

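### The Economic evaluation section bases QALYs on two SF12v2 time points although a 3-month measurement is planned elsewhere, and it states no adjustment of the QALY increment for baseline utility

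*Protocol article*

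**What the plan says.** The article places the SF12v2 in two ways.

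- Secondary outcomes, covering every secondary measure: "Secondary outcome measures will be collected at baseline, 3 and 6 months through objective measures taken by pathology collectors and a self-report telephone questionnaire". Quality of life by SF12v2 is one of the measures listed below that sentence, and its subsection names it as the QALY source: "These utility scores will be used to calculate Quality-adjusted Life Years (QALYs) for the economic evaluation".
- Economic evaluation: "Quality of life will be measured using the SF12v2 at baseline and end of trial". The same sentence goes on to the QALY calculation with the UK valuation. Month 3 is not mentioned.

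The increments are described as follows: "Using the mean costs and mean health outcomes in each trial arm, incremental costs and incremental outcomes will be determined". Uncertainty is handled by resampling: "These results will be plotted on a cost-effectiveness plane with bootstrapped estimates to present joint uncertainty in costs and health outcomes". Neither sentence mentions baseline utility. By contrast, the Statistical analysis section lists quality of life among the outcomes whose GEE models adjust for the baseline score.

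The intervention section gives the message schedule as "daily text messages for months 1–3; and four messages per week for months 4–6".

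**The concern.** One instrument has two schedules in one document, and the section that produces the QALYs uses the shorter one. With two measurements, the natural QALY calculation joins baseline and 6 months by a straight line. The intervention's intensity changes at month 3, so a utility difference that rises early and then flattens or fades is plausible. A straight line from baseline to 6 months cannot show that.

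Baseline utility also enters each person's QALY directly. A difference in unadjusted arm means would therefore carry any chance baseline difference into the incremental QALY.

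Over half a year the incremental QALY will be small, so modest errors can shift the cost per QALY and the acceptability curve. Cost-effectiveness is part of the stated aim, and the Discussion expects the findings to inform the Ministry of Health on scaling up.

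**Working it through.** **Inputs from the article.** Follow-up is 6 months (0.5 year). SF12v2 is planned at 0, 3 and 6 months (Secondary outcomes) or at 0 and 6 months (Economic evaluation). There are 170 per arm with 20% loss (Sample size), so 170 × 0.80 = 136 evaluable per arm. The article gives no QALY, utility or cost-utility figure, so there is none to reproduce.

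**Assumptions, not in the article.** QALYs are a trapezoidal area under the utility curve; utility SD is 0.10 to 0.15; the correlation ρ between baseline and 6-month utility is 0.5 to 0.7; the SD is the same at both times.

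**Step 1: weights.**

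- Two points: 0.5 × (u0 + u6)/2 = 0.25·u0 + 0.25·u6.
- Three points: 0.25 × (u0 + u3)/2 + 0.25 × (u3 + u6)/2 = 0.125·u0 + 0.25·u3 + 0.125·u6.

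The weights sum to 0.5 in both. Month 3 has half the total in the three-point area and none in the two-point area. Dropping it doubles the weight on baseline from 0.125 to 0.25.

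**Step 2: effect on the increment.** Take equal baselines, a between-arm gain g3 at 3 months and d at 6 months. The two-point increment is 0.25d and the three-point increment is 0.25·g3 + 0.125d. Their difference is 0.25 × (d/2 − g3), which is zero only when g3 = d/2. With u the full gain:

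| Path of the gain | Two-point | Three-point | Two-point ÷ three-point | Cost per QALY, two-point ÷ three-point |
|---|---|---|---|---|
| Linear (g3 = u/2, d = u) | 0.25u | 0.25u | 1.0 | 1.0 |
| Full by 3 months, held (g3 = d = u) | 0.25u | 0.375u | 0.67 | 1.5 |
| Full by 3 months, halved by 6 (g3 = u, d = u/2) | 0.125u | 0.3125u | 0.40 | 2.5 |
| Only after 3 months (g3 = 0, d = u) | 0.25u | 0.125u | 2.0 | 0.5 |

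As an illustration, an assumed d of 0.02 gives a two-point increment of 0.005 QALY. The three-point value is 0.0075 if the gain is full by 3 months and 0.0025 if it comes only afterwards.

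**Step 3: baseline imbalance.** The standard error of the between-arm difference in mean baseline utility is SD × √(2/136) = SD × 0.1213. Its direct term in the two-point QALY has weight 0.25:

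- SD 0.10: 0.25 × 0.10 × 0.1213 = 0.0030 QALY.
- SD 0.15: 0.25 × 0.15 × 0.1213 = 0.0045 QALY.

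Dividing by 0.25, these equal a 6-month utility gain of about 0.012 to 0.018 in the two-point calculation.

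Imbalance also persists into the 6-month value through ρ. A one-standard-error imbalance then moves the two-point increment by 0.25 × SD × 0.1213 × (1 + ρ). At SD 0.15 and ρ = 0.7 this is 0.0045 × 1.7 = 0.0077.

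**Step 4: what adjustment would remove.** Per person, the unadjusted two-point QALY has variance 0.0625·SD²·2(1 + ρ). After regression on baseline utility it is 0.0625·SD²·(1 − ρ²). The ratio is (1 − ρ)/2, which is 0.25 at ρ = 0.5 and 0.15 at ρ = 0.7. The standard error therefore falls to about 0.50 or 0.39 of its unadjusted value.

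**The case against.** The strongest reply is that the economic sentence says when the SF12v2 is measured, not which measurements enter the analysis. On that reading the specific statement may override the general one, and no 3-month utility would exist. This stands as far as it goes: the article does not settle whether the 3-month SF12v2 will be collected. It does not remove the conflict. The Process evaluation section already has a telephone questionnaire at 3 and 6 months, so a 3-month contact exists either way.

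Several stronger conclusions are tempting and are not supported.

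- A reader might infer that the cost-utility result is certain to be misestimated. The two areas agree if the difference grows linearly. The change in message frequency makes another path plausible but does not show one, and no direction of error follows.
- A reader might infer that raw means will be compared. The article says arm means; it does not say unadjusted. A condensed article may leave baseline adjustment to a fuller plan. What can be said is that adjustment is stated for quality of life in the effectiveness models and not in the economic section.
- A reader might infer bias from baseline imbalance. Under randomisation unadjusted differences are unbiased on average. Chance imbalance adds variance, and the planned bootstrap already carries that variance into the plane and the acceptability curve. Adjustment gains precision; it does not rescue an invalid estimate.
- A reader might infer that the HbA1c increment in the cost-effectiveness ratio will differ from the primary GEE estimate. The article does not say which HbA1c estimate enters the ratio, so this cannot be concluded.

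The area-under-the-curve method is itself an inference, since the article does not say how utilities become QALYs over time. The phrase about joint uncertainty already implies resampling each person's costs and outcomes together.

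**Conclusion.** The point holds in a limited form. The SF12v2 schedule in the Economic evaluation section conflicts with the Secondary outcomes and Quality of life sections. Followed as written, it leaves a planned measurement out of the QALY. If QALYs are areas under the curve, the incremental QALY is unaffected on a linear path. In the non-linear examples worked here it ranges from 60% too low to twice too high.

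The missing statement on baseline utility is a matter of precision. The direct baseline term alone has a standard error of about 0.003 to 0.0045 QALY, on an assumed utility SD of 0.10 to 0.15 and 136 per arm. That is close to the 0.005 QALY that an assumed 6-month gain of 0.02 would give.

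This should be corrected because cost-effectiveness is a stated aim. It concerns a secondary economic result only.

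**What to change.** 1. Amend the Economic evaluation section to agree with the Secondary outcomes and Quality of life sections, so that SF12v2 is taken at baseline, 3 and 6 months.
2. State that QALYs are the area under the utility curve through all three times: 0.125·u0 + 0.25·u3 + 0.125·u6.
3. State that the incremental QALY is estimated by regression on arm with baseline utility as a covariate, refitted within each replicate of the planned bootstrap.
4. State how missing 3-month utilities are handled, since a three-point area needs a value at that time.

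If the 3-month SF12v2 is already in the questionnaire, as the Secondary outcomes section says, the cost is a wording change, slightly more analysis work and the rule for missing values. If it is not, the 12 items must be added to a 3-month telephone questionnaire that the article already plans.

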### Sample size

The required sample size of 340 (170 per arm) will provide 80% power of detecting a between-group change in HbA1c of 0.7%, allowing for 20% loss to follow up and an alpha = 0.05.

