### Statistical analysis

Statistical analysis will be conducted using the software programs Statistical Package for the Social Sciences (SPSS-25) and Statistical Analysis System (SAS) v9.4, with an intention to treat principle.

Generalised estimating equation (GEE) models will be used to assess impact, modelling repeated outcome measures over time. Change in HbA1c will be analysed using GEE models to test the effect of the intervention on change in HbA1c between the two groups.

GEE will also be used to assess the effect of group allocation on changes over time in BMI, TC, LDL-C, HDL-C, TG, physical activity, dietary behaviour, smoking status, quality of life, self-efficacy measures and use of health services after adjusting for baseline scores. Two planned subgroup analyses will be undertaken to assess differential impact of the intervention on the basis of age and sex.

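### Incremental cost is formed from arm means with no adjustment named for pre-randomisation Medicare and pharmaceutical cost, which gives up some precision

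*Protocol article*

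**What the plan says.** In the protocol article, the Economic evaluation section takes individual costs from administrative records: "Healthcare utilisation, including doctor or specialists visits, will be determined by individual data linkage to the Medicare Benefits Schedule", and "Medicines use will be determined from the Pharmaceutical Benefits Schedule". Consent to access these records is to be sought from each participant. No start or end date for the records is given.

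The estimator is then named: "Using the mean costs and mean health outcomes in each trial arm, incremental costs and incremental outcomes will be determined". No covariate is mentioned, and the means are called neither adjusted nor unadjusted. Uncertainty is handled as follows: "These results will be plotted on a cost-effectiveness plane with bootstrapped estimates to present joint uncertainty in costs and health outcomes". A cost-effectiveness acceptability curve is added, and "Multiple one-way sensitivity analyses will be conducted around key variables".

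The Statistical analysis section treats service use differently. Its generalised estimating equation models cover, among other outcomes, "quality of life, self-efficacy measures and use of health services after adjusting for baseline scores".

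**The concern.** A participant's claims cost over six months is likely to be skewed and to follow earlier use: number of medicines, comorbidity and how often they already saw doctors. If, by chance, one arm has more heavy users at entry, a difference in arm means carries that imbalance into the incremental cost. The randomisation section describes blocks of four and mentions no stratification by prior use, so the described design does not limit this imbalance.

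The article already applies baseline adjustment to use of health services. Service use is not among the measures described under Secondary outcomes, and the only source named for it in the text is the claims linkage. The clinical model therefore appears to need a pre-randomisation record of service use, while the economic section does not mention one.

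Cost-effectiveness is part of the stated aim, and incremental cost is the numerator of both planned ratios. A less precise numerator means a wider scatter on the cost-effectiveness plane and a less decisive acceptability curve. The point concerns the cost side only, not utilities or QALYs.

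**Working it through.** **The plan's own figure.** The article gives no cost standard deviation, no correlation between prior and in-trial cost, no programme cost and no power for the cost comparison, so there is no cost figure to reproduce. The only usable input is the number randomised: "The required sample size of 340 (170 per arm) will provide 80% power". That calculation concerns HbA1c and is used here only for n = 170 per arm.

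**Assumptions (not in the article).** Coefficient of variation (CV) of six-month cost per person: 1 to 2. Correlation ρ between pre-randomisation and in-trial cost: 0.3 to 0.7. Participants are treated as independent, which ignores the couples allocated together.

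**Step 1. Precision of the difference in arm means, as a fraction of mean cost.**

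SE = CV × √(2/n), with √(2/170) = 0.108.
- CV 1: SE = 0.108; 95% half-width = 1.96 × 0.108 = 0.21.
- CV 2: SE = 0.217; 95% half-width = 1.96 × 0.217 = 0.43.

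If only 80% contributed cost data (136 per arm), √(2/136) = 0.121 and the half-widths become 0.24 and 0.48.

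**Step 2. Effect of adjusting for prior cost.**

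Adjusted SE = SE × √(1 − ρ²). Equivalent sample-size factor = 1/(1 − ρ²). Share of the variance of the difference explained by prior cost = ρ².

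| ρ | √(1 − ρ²) | SE lower by | Sample-size factor | Variance explained |
|---|---|---|---|---|
| 0.3 | 0.954 | about 5% | 1.10 | 9% |
| 0.5 | 0.866 | 13% | 1.33 | 25% |
| 0.7 | 0.714 | 29% | 1.96 | 49% |

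The proportional gain depends on ρ alone, not on the cost variance or n.

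**Step 3. The same in dollars, for an assumed SD of AUD 2,000 and 170 per arm.** Unadjusted SE = 2,000 × 0.1085 = 217. Adjusted SE is 207 at ρ = 0.3, 188 at ρ = 0.5 and 155 at ρ = 0.7.

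**Step 4. Can the imbalance be compared with the programme cost?** The part of the raw difference due to imbalance in prior cost has standard deviation ρ × SE. The chance that it exceeds an assumed programme cost per person, over SD AUD 1,000 to 5,000 and ρ 0.5 to 0.7, is:
- programme cost AUD 50: 36% to 90%;
- programme cost AUD 100: 7% to 79%;
- programme cost AUD 200: under 1% to 60%.

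The answer runs from negligible to near certain, depending on inputs the article does not give. Over the same range the SE that remains after adjustment is AUD 77 to 470, so adjustment reduces the noise without removing it.

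**The case against.** The strongest reply is that the article never calls the means raw. Adjusted arm means are also means per arm and can be computed within a bootstrap, and a condensed article may leave covariates and linkage dates to a fuller document that is not shown. That stands in part: it rules out saying that the authors rejected adjustment. It does not remove the point, because the section does name an estimator, and its plain reading is a difference in arm means. Nor can every omission be repaired later: if consent and linkage begin at randomisation, a later analysis plan cannot recover prior cost.

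Second, no error of validity is shown. This stands in full. The difference in arm means is unbiased under randomisation, and the bootstrap and acceptability curve report the uncertainty openly, though they do not reduce it.

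Third, the two sections do not strictly contradict each other: one describes models of trial outcomes over time, the other a within-trial economic comparison. That also stands. The contrast shows that "use of health services after adjusting for baseline scores" is already an accepted approach in this trial, which makes extending it to cost natural.

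Fourth, a reader might infer that the linkage leaves out the period before randomisation. The article does not say so. The window is unstated, and the study-flow figure, whose legend mentions both schemes, is not available here.

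**Conclusion.** The point holds as a modest one about efficiency. The economic section forms incremental cost from arm means and names no adjustment for pre-randomisation cost, although the trial baseline-adjusts service use elsewhere and its own linkage could supply the covariate. The loss is precision only: a standard error about 5% to 29% larger than it need be, measured as the reduction that adjustment would bring, resting on an assumed correlation of 0.3 to 0.7.

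A reader might go further and infer that chance imbalance in prior use swamps the small cost of a text-message programme, or that the cost-effectiveness plane would mainly show such imbalance. The document does not support either. It gives no programme cost, and message fees alone would understate that cost, because platform set-up, staffing and consumables are also counted. Even at a correlation of 0.7, prior cost explains 49% of the variance of the difference, which is less than half.

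**What to change.** In the Economic evaluation section:

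1. State the period that the MBS and PBS records will cover. Have the linkage request and the consent include a stated time before randomisation (for example 6 months), if they do not already.
2. Estimate incremental cost by regressing in-trial cost on arm and pre-randomisation cost, refitted in each replicate of the bootstrap already planned, so that the plane and the acceptability curve use the adjusted estimate.
3. Keep the unadjusted arm means as a descriptive table.

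The cost is small: a longer date range in the linkage request, one covariate, and possibly an amendment to the linkage application and consent wording. Participants who have already consented to a shorter window might need to re-consent, which means some extra contact. Otherwise they would lack the covariate, and the section should then say how that missing value is handled.

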### Process evaluation

Process evaluation will be conducted using survey responses and process information obtained in the telephone questionnaire by interview at 3 and 6 months. The evaluation will assess intervention acceptability based on participant satisfaction, engagement, retention and recommendations. These measures will be summarised using descriptive statistics.

